# Prospective study of oncologic outcomes after laparoscopic modified complete mesocolic excision for non-metastatic right colon cancer (PIONEER study): study protocol of a multicentre single-arm trial

**DOI:** 10.1186/s12885-020-07151-2

**Published:** 2020-07-14

**Keywords:** Modified complete mesocolic excision, Laparoscopic surgery, Right-sided colon cancer, Oncologic outcomes

## Abstract

**Background:**

The introduction of complete mesocolic excision (CME) with central vascular ligation (CVL) for right-sided colon cancer has improved the oncologic outcomes. Recently, we have introduced a modified CME (mCME) procedure that keeps the same principles as the originally described CME but with a more tailored approach. Some retrospective studies have reported the favourable oncologic outcomes of laparoscopic mCME for right-sided colon cancer; however, no prospective multicentre study has yet been conducted.

**Methods:**

This study is a multi-institutional, prospective, single-arm study evaluating the oncologic outcomes of laparoscopic mCME for adenocarcinoma arising from the right side of the colon. A total of 250 patients will be recruited from five tertiary referral centres in South Korea. The primary outcome of this study is 3-year disease-free survival. Secondary outcome measures include 3-year overall survival, incidence of surgical complications, completeness of mCME, and distribution of metastatic lymph nodes. The quality of laparoscopic mCME will be assessed on the basis of photographs of the surgical specimen and the operation field after the completion of lymph node dissection.

**Discussion:**

This is a prospective multicentre study to evaluate the oncologic outcomes of laparoscopic mCME for right-sided colon cancer. To the best of our knowledge, this will be the first study to prospectively and objectively assess the quality of laparoscopic mCME. The results will provide more evidence about oncologic outcomes with respect to the quality of laparoscopic mCME in right-sided colon cancer.

**Trial registration:**

ClinicalTrials.gov ID: NCT03992599 (June 20, 2019). The posted information will be updated as needed to reflect protocol amendments and study progress.

## Background

With the introduction of complete mesocolic excision (CME) with central vascular ligation (CVL), the outcome of colon cancer surgery has significantly improved [1–4]. CME in colon cancer surgery is a concept analogous to total mesorectal excision in rectal cancer, which is based on sharp dissection along the embryological anatomical planes with sharp separation of the visceral fascia from the parietal plane, leading to a surgical specimen with an intact coverage [2, 5]. The CME technique involves oncologic resection with careful dissection of the mesocolon along the embryological planes, resulting in the complete mobilisation of the mesocolon covered by an intact visceral fascia layer containing all blood vessels, lymphatic vessels, and lymph nodes that may contain disseminated cancer cells [1, 4]. Moreover, the method of ligating the supplying vessels at their origin (CVL) and removing the entire mesocolon has a considerable effect on locoregional recurrence and improves oncologic outcomes [1, 3]. It is well known that excision of specimens with an intact mesocolon is associated with better survival rates than excision of specimens with a defective mesocolon [3, 4].

Although Hohenberger et al. first used the term CME with CVL [2], the concept is not necessarily new because many institutions have already accepted similar concepts. In particular, many Japanese surgeons would argue that they have been performing a similar procedure, known as D3 dissection [6]. Despite sharing similar concepts, the technical details may differ between CME with CVL and Japanese D3 dissection, as demonstrated by differences in the length of resected bowels and the area of the excised mesocolon, which seem to result from different definitions of an adequate resection margin [7].

In practice, CME for right-sided colon cancer seems to be more challenging because of the complexity and variability of the central vascular anatomy than with a left-sided disease. Moreover, the original description of CME for right-sided colon cancer indicates a very aggressive procedure including complete Kocherization and extensive extra-mesocolic lymph node dissection regardless of the tumour location and stage, which translates to a higher risk of serious postoperative complications, especially when performed laparoscopically [2, 8, 9].

Recently, we have introduced a modified CME (mCME) technique for right-sided colon cancer that keeps the same principles as the original CME procedure but with a more tailored approach according to the location and stage of the tumour. This tailored approach focuses on three main points: 1) achievement of an adequate radial margin, 2) tailored lymphadenectomy according to tumour location, and 3) selective extra-mesocolic lymph node dissection [10].

Thus far, a considerable number of studies have shown favourable oncologic outcomes and short-term outcomes with the CME, mCME, and Japanese D3 types of dissection compared with conventional surgery in right-sided colon cancer [3, 6, 10, 11]. However, to the best of our knowledge, no study has proven the oncologic safety of the laparoscopic approach with objective surgical quality assessment.

This is a multi-institutional, prospective, single-arm study designed to evaluate the oncologic outcomes after laparoscopic mCME for adenocarcinoma arising from the right side of the colon, which is defined as from the caecum up to the proximal half of the transverse colon. In this study, the participating surgeons are assumed to have overcome their learning curve and will be evaluated beforehand by independent experts. The surgical quality will be assessed on the basis of both, the resected surgical specimen and the operation field after specimen removal, using submitted photographs.

## Methods

### Study design

This is a multi-institutional, prospective, single-arm study. The duration of the study will be approximately 5 years (2 years of inclusion, 3 years of follow-up). Patients will be enrolled at five tertiary colorectal cancer centres in South Korea, including Yonsei Cancer Center, Seoul National University Hospital, St. Vincent’s Hospital, Kyungpook National University Chilgok Hospital, and Korea University Anam Hospital. A complete information leaflet will be provided to the patients during the first consultation, and informed consent will be obtained from them after screening. The preoperative, intraoperative, and postoperative periods will be in complete accordance with the usual care practices of the centres. The baseline demographics and conditions, as well as the perioperative details and the postoperative occurrences, will be recorded on a previously designed case report form. Data from each participating hospital will be collected at the PIONEER database. Data collection forms can be assessed after login on the website. Each hospital has access to their own dataset. The follow-up encompasses 13 postoperative consultations: 1 month, 3 months, and every 3 months thereafter until 36 months.

### Ethics approval

Before the enrolment of the first patient, approval for this study will be obtained from the institutional review board of each participating research centre (five tertiary hospitals) in South Korea. Written informed consent will be obtained from all patients for the acquisition and use of anonymised clinical data before they are recruited, and all investigators will conduct this study in accordance with the tenets of the Declaration of Helsinki. This study will be monitored by an independent data and safety monitoring committee.

### Study population

Patients with adenocarcinoma arising from the right side of the colon who are indicated to undergo a laparoscopic mCME will be eligible for this study. The right side of the colon is defined as from caecum up to the proximal half of the transverse colon. Investigators from each institution will be responsible for the enrolment according to the inclusion/exclusion criteria and patient conditions. The flow of participant inclusion is schematically shown in Fig. 1.

**Fig. 1 Fig1:**
[figure not shown]
Flow chart of the study

### Inclusion criteria

Qualitative diagnosis: a pathological diagnosis of adenocarcinoma, with the tumour located between the caecum and the proximal half of the transverse colonSuitability for curative surgery and age > 19 yearsAmerican Society of Anesthesiologists physical status grade I-IIINo preoperative treatmentProvision of written informed consent

### Exclusion criteria

Need for an emergency operation because of conditions such as perforation or malignant colonic obstructionPreoperative imaging examination results showing distant metastasisHereditary colon cancerHistory of any other malignant tumour in the recent 5 years, except for cervical carcinoma in situ that has been cured, basal cell carcinoma, or squamous cell carcinoma of the skinSimultaneous or simultaneous multiple primary colorectal cancerPregnancy or breastfeeding in womenPatients who are not suitable to undergo laparoscopic surgery (due to, e.g., extensive adhesion caused by prior abdominal surgery, inability to endure artificial pneumoperitoneum, etc.)Refusal to provide informed consent

### Sample size considerations

On the basis of previous data, the median 3-year disease-free survival (DFS) rate after CME for right-sided colon cancer is estimated to be approximately 80%, and the null hypothesis is a 3-years DFS rate after laparoscopic mCME for right-sided colon cancer of at least 88% [12, 13]. This will be assessed using an exact *p*-value of 0.025 and a power of 0.90 based on the Clopper-Pearson method. Thus, the sample size is 225. The total sample size is set to 250, considering a maximum dropout rate of about 10% for this clinical study.

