### Endpoints

#### Primary endpoint

The primary endpoint is 3-year DFS, calculated as the time from surgery until the first objective documentation of recurrence or death from any cause.

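### A time-to-event primary endpoint is to be assessed with an exact binomial method that cannot use censored follow-up, and the handling of losses decides whether 90% power is kept

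*Protocol article*

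**What the plan says.** Under Primary endpoint, 3-year DFS is "calculated as the time from surgery until the first objective documentation of recurrence or death from any cause".

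Under Sample size considerations, the article gives these elements:

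- Reference: "the median 3-year disease-free survival (DFS) rate after CME for right-sided colon cancer is estimated to be approximately 80" per cent.
- Hypothesis: "the null hypothesis is a 3-years DFS rate after laparoscopic mCME for right-sided colon cancer of at least 88" per cent.
- Test: "This will be assessed using an exact *p*-value of 0.025", with "a power of 0.90 based on the Clopper-Pearson method".
- Size: "Thus, the sample size is 225". Then: "The total sample size is set to 250, considering a maximum dropout rate of about 10% for this clinical study".

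The article does not say how a patient lost before 36 months enters the primary analysis, or when losses are expected. It names no Kaplan-Meier or other method that handles censoring.

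**The concern.** The sentence on the test goes beyond sizing, because it says how the hypothesis will be assessed. Clopper-Pearson needs a yes/no status at 36 months for everyone in the denominator. A patient lost event-free at month 8 has no such status, whereas a patient who recurs at month 8 does. The method therefore forces a choice: remove the losses, count them as disease-free, or count them as failures.

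The step from 225 to 250 treats losses as contributing nothing, which points towards removal. Removal takes out only patients without an observed event, so the remaining proportion is biased downward. At stake are the power and error rate of the only formal test in a single-arm trial, and a choice that could otherwise be made after the results are known.

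**Working it through.** **Inputs from the article:** 80% and 88%; 0.025; power 0.90; 225 evaluable; 250 enrolled; at most about 10% dropout.

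**Assumptions, not in the article:** exponential event times; dropout independent of events; loss of 2% to 10%; timing from all at month 0 to all just before month 36.

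**1. The plan's own figure.** Exact binomial, null 0.80, alternative 0.88, one-sided 0.025, n = 225. The rule is at least 192 disease-free:

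- P(X ≥ 192 | 0.80) = 0.0245
- P(X ≥ 192 | 0.88) = 0.906

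225 is the smallest n that reaches 90%, and 225 / 0.9 = 250. With the hypotheses as literally worded (null 0.88, alternative 0.80), power at 225 is 89.6% and the smallest n is 215. So 225 reproduces only with 80% as the null.

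**2. Losses removed, observed events kept.** Over 36 months let a = −ln(0.88) = 0.1278 and b = −ln(0.90) = 0.1054.

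- Event-free and followed: 0.88 × 0.90 = 0.792
- Observed events: a/(a + b) × (1 − 0.792) = 0.114
- Lost: 1 − 0.792 − 0.114 = 0.094
- Expected proportion among those kept: 0.792 / (0.792 + 0.114) = 0.874, against a true 0.880

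Power is averaged over a random number n of evaluable patients, n ~ Binomial(250, 1 − lost), with the exact rule for each n. It is 83.3%, or 82.6% if b is set so that observed loss is exactly 10%. With exactly 225 evaluable in that latter case it is 84.7%. The same steps at true DFS 0.80 give an expected proportion of 0.791 and type I error of about 0.9% (0.8% to 1.0% across these variants).

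**3. Range by amount and timing of loss** (losses removed, true DFS 0.88):

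| Loss | Timing | Expected proportion | Power, random n |
|---|---|---|---|
| 2% | constant hazard | 0.879 | 90.8% |
| 5% | constant hazard | 0.877 | 88.0% |
| 10% | constant hazard | 0.874 | 82.6% |
| 10% | all at month 0 | 0.880 | 89.1% (90.6% with n = 225) |
| 10% | all just before month 36 | (0.88 − 0.10)/0.90 = 0.867 | 73.2% (75.8% with n = 225) |

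**4. The other two binomial choices** (250 in the denominator, rule at least 213, hazard b as in step 2).

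- Lost counted as disease-free, true DFS 0.80: with a = 0.2231, observed events are 0.2231/0.3285 × (1 − 0.72) = 0.190, so the apparent rate is 0.810 and type I error is 0.049.
- Lost counted as failures, true DFS 0.88: the apparent rate is 0.792 and power is 0.010.

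**5. Kaplan-Meier at 36 months on all 250.** Simulation, 20,000 runs, 10% dropout; success if the lower two-sided 95% log(-log) limit exceeds 0.80. Mean estimate 0.880, power 90.2%, type I error about 0.02.

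**The case against.** The strongest reply is that the article nowhere says dropouts are removed. Raising 225 to 250 is a planning step and is compatible with analysing all 250. Censoring rules commonly sit in a full protocol or analysis plan, neither of which is shown. The stated power is also right for its own inputs. Study design and Follow-up plan three years of observation for every patient, so there is little administrative censoring before the landmark. A binomial test at a fixed time is then not wrong in itself, because only true losses matter. Some losses may fall at or near surgery, for example when exploration finds metastasis, and these do not cause the bias.

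Most of this stands. A reader might infer that the protocol deletes dropouts and that its true power is 83% rather than 90%. The documents support neither. Deletion is inferred from the inflation; 83% needs the full 10% loss at a constant hazard; and 10% is given as a maximum. The two alternative ways of counting losses are not in the article either; they only show what the stated method leaves open.

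What the reply does not remove is the mismatch. The article names a method of assessment that cannot use censored follow-up, for an endpoint defined as a time. An analysis plan that handled censoring properly would have to depart from that sentence.

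**Conclusion.** The point holds as a mismatch between endpoint and stated method, not as a miscalculated sample size. With known status for 225 patients, power is 90.6%. If event-free losses are removed, 10% constant-hazard dropout costs about 0.6 percentage points in the estimate and takes power to about 83%. Across the losses and timings considered, power is about 73% to 91%. Removal errs against the procedure and cannot inflate the false-positive rate. Counting losses as disease-free can, roughly doubling it from 0.025 to 0.049. These figures rest on exponential events and independent dropout, and on dropout timings that the article does not give.

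This deserves a correction of wording; it does not invalidate the design. The same section also words the null as 88% or more, although its sample size works only with 80% as the null. That needs correcting at the same time, because the success criterion depends on it.

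**What to change.** 1. Name the primary analysis: the Kaplan-Meier estimate of DFS at 36 months in all operated patients, with losses censored at the last disease assessment.
2. Use a two-sided 95% log(-log) interval and compare its lower limit with the 80% reference.
3. State that 80% is the null and 88% the alternative, and that 0.025 is one-sided.
4. Keep Clopper-Pearson on patients with known 36-month status as a sensitivity analysis, and say how losses are treated in it.

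The cost is wording in the protocol and analysis plan. No extra patients are needed, since the planned 250 keep about 90% power at 10% dropout. The drawback is an asymptotic rather than exact interval; in the simulation its type I error stayed below 0.025.

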### Endpoints

#### Primary endpoint

The primary endpoint is 3-year DFS, calculated as the time from surgery until the first objective documentation of recurrence or death from any cause.

#### Secondary endpoints

The 3-year overall survival, calculated as the time from surgery until a documented death from any causeIncidence of postoperative morbidity until 4 weeks after surgeryCompleteness of mCME, assessed by reviewing the resected surgical specimen primarily by the pathologist at each centre and secondarily by central reviewers based on specimen photographsCentral radicality, assessed by reviewing the operative field after specimen removal primarily by the attending surgeon at each centre and secondarily by central reviewers based on photographs obtained during the procedureDistribution of metastatic lymph nodes, assessed by categorising the lymph nodes retrieved from resected surgical specimens

### Participating surgeons

The participating surgeons should meet the following qualifications:
Has completed at least 50 cases of laparoscopic mCME in the last 3 years.Has passed the blind review of surgery video. Briefly, the applicants will provide videos of laparoscopic mCME performed in the last 3 months (three cases each) to the Research Council. The Research Council will select two videos of laparoscopic mCME separately and randomly appoint three experts to perform a blind peer review. When more than two experts unanimously approve, the applicant will be permitted to participate in this study as a researcher.

### Surgical technique

Laparoscopic mCME will be carried out with endotracheal intubation under general anaesthesia. The surgeon should explore the abdominal cavity to determine if there is any distant metastasis, including hepatic, peritoneal, mesenteric, or pelvic metastasis. Thereafter, laparoscopic mCME will be performed in either a lateral-to-medial or medial-to-lateral fashion, according to the surgeon’s preference.

Similar to the original CME procedure, mCME requires the separation of the visceral fascia from the parietal fascia by sharp dissection and by ligating the supplying vessels at their origin.

Unlike the original CME, which performs consistent surgery regardless of the location of the right colon cancer, mCME has a tailored approach depending on the tumour location (Table 1).

**Table 1 Tab1:** CME vs. Japanese D3 vs. mCME

	The original CME [2–4]	Japanese D3 [6, 14]	mCME [10]
**Dissection plane**	Embryologic tissue plane between retroperitoneal fascia and mesocolic fascia	Along with the layers of fusion fascia	Embryologic tissue plane respected, but obtaining secure radial margin weighed more
**Tailored lymphadenectomy**	Not mentioned	Tailored according to tumor location and stage	Tailored according to tumor location and stage
**Extra-mesocolic lymphadenectomy**	Recommended	Not recommended	Not recommended
**Securing radial margin**	Not clearly mentioned	Not clearly mentioned	Very important
**Surgical quality assessment**	Specimen grading, morphometry	Not clearly mentioned	Specimen grading as well as surgical field photo documentation after specimen removal
**Proximal & distal resection margin**	Not mentioned, but wide enough bowel resection length	10-cm rule	Bowel resection length determined by tailored lymphadenectomy

^a^ Gastroepiploic, gastrocolic trunk nodes, lymphatic tissue in pancreas capsule and other lymph nodes that are not contained in mesocolon

First, although complete Kocherization is mandatory in the original CME description, it may be required to clear a possible tumour spread if the tumour is infiltrating or adhering to the duodenum or perinephric fat tissue. Second, if the tumour is locally advanced, the entire prerenal soft tissue behind Gerota’s fascia may need to be cleared, especially for tumours growing toward the posterior. The third difference of mCME from the conventional CME involves the tailored resection of the mesocolon and ileal mesentery according to the tumour location. After identifying the root of the middle colic artery, the site of the vascular ligation depends on the location of the tumour (Fig. 2). When the tumour is located in the caecum and ascending colon, only the right branch of the middle colic artery is ligated. If the tumour is present in these latter sites, the root of the middle colic artery is ligated. If the tumour is located in the proximal ascending colon or caecum, enough distal ileum branches of the superior mesenteric artery (SMA) are needed in the specimen to obtain a longer distal ileum. As a result, the length of the distal ileum is determined by the extent of mesenteric dissection in the mCME procedure.

**Fig. 2 Fig2:**
[figure not shown]
Overview of the modified complete mesocolic excision procedure with the site of the vascular ligation depending on the location of the tumour (red arrow) and the level of central radicality (blue arrow). **a** Ascending colon cancer: only the right branch of the middle colic artery is ligated. Lymphadenectomy around the origin of the colic artery with complete exposure of the superior mesenteric vein (SMV). **b** Proximal transverse colon cancer: the root of the middle colic artery is ligated. Lymphadenectomy around the origin of the colic artery with complete exposure of the SMV and the superior mesenteric artery (SMA)

### Photographic documentation

The submission of three photographs is required. We will perform a central review of the surgical procedure by evaluating the photographs obtained during the procedure for all patients. The study-specific committee will evaluate these photographs for quality control and surgical assessment, and the surgical procedure will be discussed at group meetings planned to be held twice a year. Either film or digital cameras will be used to obtain the photographs.
Reviewing the operative field after lymph node dissection and specimen removal based on photographs (Fig. 3)A photograph displaying the central radicality (extent of lymphadenectomy) will be obtained between the time after ‘lymphadenectomy and ligation of feeding arteries’ and before ‘anastomosis’.2.Reviewing resected surgical specimens based on photographs (Fig. 4)High-resolution digital colour photographs of fresh specimens will be taken immediately after resection.Photographs of the front and back sides of the unfixed, unopened specimens, placed alongside a metric scale, will be taken.The mesentery must be laid out flat without stretching, and the site of the tumour and high vascular ties (HVTs) should be identifiable.

